### Data Collection and Management

All our measures will be free of charge to ensure complete participation in the follow-up evaluation. Case report forms will be completed in paper form and stored by the Shanghai University of Traditional Chinese Medicine. Data will be collected according to Table 1 by investigators, and personal information about the enrolled participants will be kept in Yueyang Hospital in order to protect confidentiality in the whole trial. The ethics committee of Yueyang Hospital affiliated with the Shanghai University of Traditional Chinese Medicine will audit the trial every 12 months and will establish a data monitoring committee, which is independent from the funder and has no competing interests. The data will be stored in the clinical trial public management platform and ready for public inquiry after the trial. A quality control group independent from the research team will be set up to control the quality of this study.

### Sample Size

Our previous study indicated that 58.5% of patients with BPI showed improvements in upper extremity function and muscle strength [23]. In this clinical trial, the rate of upper extremity function recovery is expected to be 75% in the naprapathy group and 55% in the physical therapy group. With α=.05 and β=.01, a total of 52 participants will be needed, as calculated using SPSS software (version 21.0; IBM Corp). According to the previous study, a 10% withdrawal rate will also be considered; therefore, each group will include at least 58 participants.

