**Methods:**

This will be a single-center randomized controlled trial. A total of 116 eligible patients with brachial plexus injury will be randomly divided into an experimental group (naprapathy plus physical therapy group) or a control group (physical therapy group). The participants will be followed up for 4 weeks of treatment. Observation outcomes will include the visual analog scale score, upper limb index, electromyography findings, and adverse reactions, among others. The measuring points for outcomes will be the baseline and the completion of treatment. In addition, a quality control group independent from the research team will be set up to control the quality of the trial. Finally, the data will be analyzed using SPSS software (version 21.0; IBM Corp).

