### Randomization

In this clinical trial, a total of 116 participants with BPI will be randomly assigned to either group A (naprapathy plus physical therapy) or group B (physical therapy) at a 1:1 ratio. The random sequence will be generated using SAS software (version 9.3; SAS Institute, Inc). The coauthors randomizing the participants are not linked to any statistical work.

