### Statistical Analysis

All data will be analyzed by researchers using SPSS (version 21.0) software. Data will be expressed as the mean (SD) or median (IQR). First, the data will be tested for normality and homogeneity of variance; if the data meet the requirements for a normal distribution, the homogeneity of variance will be analyzed by the *F* test. In the case of heterogeneity, the corrected *t* test will be used. If the requirements for normality and homogeneity of variance are not satisfied, the rank-sum test will be used. If the sphericity test yields a *P* value less than .05, indicating that the assumption of sphericity is violated, we will perform multivariate analysis. A statistically significant result (*P*<.05) for the time factor will indicate that the measurements show a trend of changing over time. A statistically significant (*P*<.05) interaction between time and group will indicate that in addition to the effect of time, there are differences between the groups. If a *P* value is less than .05, the difference will be considered statistically significant, indicating a difference in the results between the two groups. If a *P* value is greater than .05, then the difference will not be considered statistically significant, indicating no difference in the results between the two groups. Cohen *d* (sample size) will also be used to compare differences between groups, and the generalized linear model will be applied to explore differences in outcomes between groups.

For safety analysis, adverse event data are generally expressed as the number of events and the percentage of cases involved in the adverse event.

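### The sample size does not deliver the stated β=.01: 75% vs 55% needs about 204 per group, and the 52 per group actually used gives about 57% power

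*Protocol article*

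**What the plan says.** All inputs but one stand in the Sample Size section of the protocol article. On the rates: "the rate of upper extremity function recovery is expected to be 75% in the naprapathy group and 55% in the physical therapy group". On the error levels and the result: "With α=.05 and β=.01, a total of 52 participants will be needed, as calculated using SPSS software". On the allowance for withdrawal: "a 10% withdrawal rate will also be considered; therefore, each group will include at least 58 participants".

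The Randomization section sets the allocation: "group A (naprapathy plus physical therapy) or group B (physical therapy) at a 1:1 ratio". The abstract gives the overall number: "A total of 116 eligible patients with brachial plexus injury will be randomly divided".

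The Sample Size section does not say whether α is one- or two-sided. The Statistical Analysis section refers only to a difference between groups: "If a *P* value is less than .05, the difference will be considered statistically significant".

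**The concern.** A β of .01 means 99% power, which is a demanding target for a 20-point difference between two proportions in the middle of the scale. A requirement of 52, per group or in total, is far too small for it. The text also calls 52 a total and in the next sentence treats it as the number per group.

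The stake is how a negative result would be read. The Statistical Analysis section takes P above .05 as showing that the groups do not differ. Beside a published type II error of 1%, a reader would treat such a result as close to conclusive for the planned effect. If the real type II error is near 43%, that reading is unsafe. This calculation is also the only justification the article gives for enrolling 116.

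**Working it through.** **Inputs.** p₁ = .75, p₂ = .55, α = .05, β = .01 and 10% withdrawal (Sample Size); 1:1 allocation (Randomization). Two-sided testing is assumed, and one-sided testing is checked as well.

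**1. The plan's step from 52 to 116.** 52/(1 − 0.10) = 57.8, rounded up to 58; 2 × 58 = 116. This reproduces the plan only if 52 is per group. If 52 were the total, the same step would give 58 participants in all, half the planned number.

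**2. The plan's 52.** The pooled normal formula per group is

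n = [z(1−α/2)·√(2p̄(1−p̄)) + z(1−β)·√(p₁(1−p₁) + p₂(1−p₂))]² / (p₁−p₂)²

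with p̄ = .65. The two square roots are √(2 × .65 × .35) = .6745 and √(.1875 + .2475) = .6595.

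For β = .01: (1.960 × .6745 + 2.326 × .6595)² / .04 = (1.322 + 1.534)² / .04 = 204.0. That is 204 per group and 408 in total. With 10% withdrawal it becomes 204/0.9 = 226.7, so 227 per group and 454 in total.

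Other readings of the same inputs, per group (pooled formula):

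| β | Two-sided .05 | One-sided .05 |
|---|---|---|
| .01 | 204 | 175 |
| .10 | 118 | 96 |
| .20 | 89 | 70 |

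At β = .01, the unpooled, arcsine and continuity-corrected versions, one- and two-sided, all lie between 172 and 214 per group. Exchanging α and β (α = .01, β = .05) gives 200 two-sided and 177 one-sided. With the stated rates, a value near 52 appears only at much lower power with a one-sided test: 53 per group at 70%, or 51 with continuity correction at 60%. The stated figure could not be reproduced.

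**3. Power the trial has for these rates.**

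Power = Φ{[(p₁−p₂)·√n − z(1−α/2)·√(2p̄(1−p̄))] / √(p₁(1−p₁) + p₂(1−p₂))}

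For n = 52: (.20 × 7.211 − 1.322)/.6595 = .182, and Φ(.182) = .572.

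| Evaluable per group | Two-sided | One-sided |
|---|---|---|
| 26 (52 as a total) | 32.3% | 44.6% |
| 52 | 57.2% | 69.3% |
| 58 (no withdrawals) | 62.0% | 73.5% |

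Exact enumeration at 52 per group gives 58.5% for the uncorrected chi-square test and 49.9% for Fisher's test, both two-sided.

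**4. Difference that 52 per group can detect.** With the comparison rate at 55%, the same formula gives 80.3% power for 80.5% vs 55%, a difference of about 25 points.

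**5. Sensitivity to the control rate.** The section cites 58.5% improvement in an earlier study but plans on 55%. With 75% kept in the naprapathy group and 58.5% in control, power at 52 per group is about 43%, and 80% power needs 127 per group. If the 20-point difference is kept instead (78.5% vs 58.5%), power is about 60% and 99% power needs about 193 per group.

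**The case against.** The arithmetic itself cannot be rebutted. The objections concern what is built on it.

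- **Sidedness is assumed.** True, and it should be labelled as such. A one-sided test still needs 175 per group and gives 69% power at 52, so the conclusion stands.
- **The 32% figure describes a trial nobody is running.** This is fair. The plan's own step to 58 per group shows that 52 was meant per group. The figure matters only for a reader who takes the printed words literally.
- **The 58.5% comparison is weak.** This is also largely fair. The article does not say that those patients received the control treatment, and it describes improvement in function and muscle strength where the planning rate is functional recovery. The effect on power goes either way, depending on whether 75% or the 20-point gap is held fixed. It is a sensitivity point, and the conclusion does not rest on it.
- **The primary outcome is the change in visual analog scale score, not a recovery rate.** This is correct, and it limits the finding: 57% is the power for the binary endpoint used for sizing, and the article gives no power for the primary test. That is a separate gap. It does not make the stated β true for the rates to which it is attached.
- **The authors should first be asked how 52 was obtained.** That is reasonable, but no answer can reconcile 52 with the inputs as printed.

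**Conclusion.** The concern holds. For 75% vs 55% at α = .05 and β = .01 the requirement is about 204 per group two-sided (175 one-sided), roughly four times the 52 used. On the plan's own rates, 52 evaluable per group gives about 57% power (69% one-sided), so the type II error is about 43% instead of 1%. No conventional reading of β rescues the figure. Separately, calling 52 a total contradicts the plan's own 58 per group and 116 overall.

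The result rests on the stated rates, 1:1 allocation and a standard comparison of two proportions. The power figures add the assumption of two-sided testing and apply only to the recovery rate on which the trial was sized.

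**What to change.** Keep 116 participants and correct the Sample Size section:

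- Replace the total of 52 with 52 per group (104 evaluable), rising to 58 per group and 116 in all with 10% withdrawal.
- Delete β = .01.
- State that α is two-sided, if that is the intention, and that 52 evaluable per group gives about 57% power for 75% vs 55%, and 80% power only for about 80.5% vs 55%.
- Say that these figures refer to the recovery rate, so that they are not taken as the power for the visual analog scale outcome.

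The cost is a change of wording and a less favourable power statement. No patients are added and the design does not change. The article reports 100 of the 116 enrolled by January 2023, so restating the power is more practical than enlarging the trial to the 454 that the printed β would require.

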### Statistical Analysis

All data will be analyzed by researchers using SPSS (version 21.0) software. Data will be expressed as the mean (SD) or median (IQR). First, the data will be tested for normality and homogeneity of variance; if the data meet the requirements for a normal distribution, the homogeneity of variance will be analyzed by the *F* test. In the case of heterogeneity, the corrected *t* test will be used. If the requirements for normality and homogeneity of variance are not satisfied, the rank-sum test will be used. If the sphericity test yields a *P* value less than .05, indicating that the assumption of sphericity is violated, we will perform multivariate analysis. A statistically significant result (*P*<.05) for the time factor will indicate that the measurements show a trend of changing over time. A statistically significant (*P*<.05) interaction between time and group will indicate that in addition to the effect of time, there are differences between the groups. If a *P* value is less than .05, the difference will be considered statistically significant, indicating a difference in the results between the two groups. If a *P* value is greater than .05, then the difference will not be considered statistically significant, indicating no difference in the results between the two groups. Cohen *d* (sample size) will also be used to compare differences between groups, and the generalized linear model will be applied to explore differences in outcomes between groups.

For safety analysis, adverse event data are generally expressed as the number of events and the percentage of cases involved in the adverse event.

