### Outcomes

#### Primary Outcome Indicator

The primary outcome measure will be the change in visual analog scale score relative to baseline at 4 weeks.

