### Time Points of Outcome Measurement

Outcomes will be evaluated at 2 time points: baseline and at the completion of treatment. An overview of the outcomes measured at the different time points is shown in Table 1.

**Table 1 table1:** Case data collection timetable.

Time point	Baseline	Posttreatment
Written informed consent	✓	
Concomitant treatment	✓	
Disease history	✓	
History of medication	✓	
Brunnstrom functional assessment	✓	✓
VAS^a^	✓	✓
EMG^b^ examination	✓	✓
Participant self-evaluation		✓
Adverse events		✓
Safety analysis		✓

^a^VAS: visual analog scale.

^b^EMG: electromyography.

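### No single primary test is fixed for change in VAS: the t and rank-sum rules overlap or leave a gap, the sphericity rule is void, and baseline VAS is not a covariate

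*Protocol article*

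**What the plan says.** The Primary Outcome Indicator section fixes the endpoint: "The primary outcome measure will be the change in visual analog scale score relative to baseline at 4 weeks". Time Points of Outcome Measurement fixes the schedule: "Outcomes will be evaluated at 2 time points: baseline and at the completion of treatment". Table 1 lists VAS at both visits.

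The Statistical Analysis section then gives these rules for all data, without saying which result decides the primary comparison:

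- Pretests: "First, the data will be tested for normality and homogeneity of variance". Normal data go on to an F test of the variances.
- Unequal variances: "In the case of heterogeneity, the corrected *t* test will be used".
- Next sentence: "If the requirements for normality and homogeneity of variance are not satisfied, the rank-sum test will be used".
- Repeated measures: a significant sphericity test is read as "indicating that the assumption of sphericity is violated, we will perform multivariate analysis", and a significant "interaction between time and group will indicate that in addition to the effect of time, there are differences between the groups".
- Finally, "the generalized linear model will be applied to explore differences in outcomes between groups", with no covariates named.

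**The concern.** The plan should settle in advance which P value and which estimate answer the primary question. Here the data choose between a t test, a corrected t test and a rank-sum test, and the choosing rule is not complete. The t tests compare mean changes and the rank-sum test compares ranks, so the quantity being estimated can change with the pretest result.

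The sphericity sentence belongs to a design with three or more measurements. The repeated-measures interaction adds nothing beyond a change-score t test, and neither uses baseline VAS in the most efficient way.

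The trial is open-label, and the analysis is done by researchers in SPSS. Freedom over the deciding test would weaken the credibility of a positive result, and the change-score comparison gives up precision that the collected data already offer.

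**Working it through.** **1. The branches.** Cross the two pretest results and read the rules against each cell:

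| Pretest result | If either failure triggers rank-sum | If both must fail |
|---|---|---|
| Normal, equal variances | t test | t test |
| Normal, unequal variances | corrected t **and** rank-sum | corrected t |
| Non-normal, equal variances | rank-sum | **no rule** |
| Non-normal, unequal variances | rank-sum | rank-sum |

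Each reading leaves one cell unresolved.

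**2. Sphericity.** Sphericity means that all pairwise differences between times have equal variance. With k times there are k(k−1)/2 differences. For k = 2 this is 1, so there is nothing to compare. Epsilon computed numerically for two levels was exactly 1. The rule can never trigger.

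**3. The interaction.** With two times, the time-by-group contrast is the difference between arms in (post − baseline). In a simulated data set the interaction F was 0.010884 and the squared t on change scores was 0.010884. They are the same test.

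**4. Type I error.** The plan gives no figure to reproduce on this point. The simulation used 5,000 null trials per scenario, 52 per arm, equal variances, and normal, bounded integer VAS or skewed data, with baseline-to-post correlation ρ of .3, .5 or .7. The Sample Size section prints 52 as a total, but 52/0.9 = 57.8, which rounds up to its 58 per group. So 52 is taken here as evaluable patients per arm.

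| Procedure | Null rejection, range over scenarios |
|---|---|
| Change-score t test | 4.7–5.4% |
| Rank-sum on change | 4.6–5.5% |
| Pretests; corrected t if normal but unequal, rank-sum if non-normal | 4.7–5.4% |
| Pretests; rank-sum if either fails | 4.7–5.4% |
| ANCOVA | 4.4–5.3% |
| Smaller P of t and rank-sum | 5.6–7.0% |
| Same, plus ANCOVA | 7.2–9.4% |
| Same, plus t test on post scores | 9.7–12.1% |

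The Monte Carlo standard error at 5% is √(0.05 × 0.95/5000) = 0.3 points, so the single tests and both pretest sequences are compatible with 5%. Data fell in the disputed cell (normal, unequal variances) in 0.04% to 5.0% of these trials.

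**5. Precision.** Let σ be the SD of one VAS measurement. The change score has variance 2σ²(1−ρ). ANCOVA has residual variance σ²(1−ρ²). The ratio is (1+ρ)/2, which is below 1 for every ρ < 1.

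Power for a difference of 0.5σ with 52 per arm, two-sided .05, is Φ(0.5 × √26/√v − 1.96), where v is the variance in units of σ² and √26 = 5.099:

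| ρ (assumed) | v, change | v, ANCOVA | Ratio | Power, change | Power, ANCOVA |
|---|---|---|---|---|---|
| .3 | 1.40 | 0.91 | 0.65 | 57.7% | 76.2% |
| .5 | 1.00 | 0.75 | 0.75 | 72.2% | 83.7% |
| .7 | 0.60 | 0.51 | 0.85 | 90.8% | 94.6% |

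For example, at ρ = .5 the change-score value is Φ(2.550 − 1.96) = Φ(0.590) = 72.2%, and the ANCOVA value is Φ(2.944 − 1.96) = Φ(0.984) = 83.7%.

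**The case against.** The strongest reply is that this is familiar, loosely drafted boilerplate. The paragraph covers all outcomes, so several methods are to be expected. Read in sequence (normality, then variances, then corrected t, otherwise rank-sum), it gives a workable scheme. The generalized linear model is labelled as exploration, the sphericity sentence is inert, a change-score analysis is valid under randomization, and covariates are often left to an analysis plan that is not shown.

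Much of this stands. The generalized linear model is not a rival confirmatory test, the sphericity error cannot alter a result, and ANCOVA is a gain in efficiency rather than a repair of bias. What does not stand is that a fuller document would settle the matter. The branch and sphericity rules are written down here, and a later plan would have to override them.

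Four stronger readings are tempting, and the protocol does not support them:

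- *The plan ignores baseline VAS.* It does not. Baseline enters by subtraction, through the endpoint and through the interaction.
- *The pretests inflate type I error.* Followed mechanically, they did not do so in the equal-variance scenarios. The higher rates require picking the best result, which the plan does not propose. The highest also require a baseline-adjusted model and a post-score t test, and the plan names neither for this outcome.
- *The trial is underpowered for VAS.* The Sample Size section plans on a binary rate of upper extremity recovery, which says nothing about power for VAS.
- *Injury type can be added as a covariate at no cost.* The Naprapathy section uses it to direct a treatment that the control arm does not receive, and Table 1 does not list it as collected.

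**Conclusion.** The point holds in a limited form. No test is designated for the primary outcome, the corrected-t and rank-sum rules overlap on one reading and leave a gap on the other, and the sphericity rule is void. Baseline VAS is used only by subtraction.

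The type I error at stake is modest: about 5% if one sequence is followed, about 6–7% if the better of t and rank-sum is reported, and about 12% as an outer bound using tests not in the plan. The simulations cover equal variances only.

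The gain from ANCOVA over change scores is a variance ratio of (1+ρ)/2 and, under the assumptions above, between about 4 and 18 points of power. That a gain exists for any ρ below 1 is algebra. Its size rests on ρ and the 0.5 SD effect, both assumed. The paragraph should be corrected before the data are analysed, but the trial's validity does not hang on it.

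**What to change.** Rewrite the paragraph to name one primary analysis: ANCOVA of 4-week VAS on treatment with baseline VAS as covariate and robust standard errors, reporting the adjusted mean difference with its 95% CI and P value. The estimated treatment effect is the same whether the dependent variable is 4-week VAS or change, so the stated endpoint is preserved.

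Delete the selection of tests by normality and variance pretests, and delete the sphericity and multivariate sentence. Keep the rank-sum test as a labelled sensitivity analysis. Add injury type as a second covariate only if it is recorded at baseline in both arms.

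The cost is one paragraph, dated before the data are analysed and reported to the ethics committee as a change to the protocol. VAS is already collected at both visits. The generalized linear model that the plan names, with normal errors and identity link, gives this ANCOVA once baseline VAS is entered, so no new data are needed.

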**Conclusions:**

One limitation of this trial is that we will be unable to achieve strict double-blinding because of the features of naprapathy. The trial aims to contribute reliable evidence for decision-making in naprapathy for treating brachial plexus injury.

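### The plan reads P>.05 as showing no difference between the groups, which a superiority test without an equivalence margin cannot show

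*Protocol article*

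**What the plan says.** The Statistical Analysis section gives a two-sided reading of the P value. Below .05, the groups are said to differ. Above .05, "then the difference will not be considered statistically significant, indicating no difference in the results between the two groups". The sentence is not tied to one outcome or one test. The same paragraph adds Cohen *d* and a generalized linear model to explore group differences, but attaches neither to the reading of a non-significant result.

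The outcomes that the rule would reach are set in the Outcomes section. For the primary one, "The primary outcome measure will be the change in visual analog scale score relative to baseline at 4 weeks". The secondary ones are the Brunnstrom upper limb motor score and EMG findings.

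The Sample Size section is built on a different quantity, a recovery rate that "is expected to be 75% in the naprapathy group and 55% in the physical therapy group". It continues: "With α=.05 and β=.01, a total of 52 participants will be needed". It then allows for 10% withdrawal, so that "each group will include at least 58 participants".

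**The concern.** A test of no difference that fails to reach P<.05 says only that the data do not exclude zero. It does not say that they exclude a worthwhile effect. To conclude that two groups do not differ in any way that matters, a plan must name a margin and show that the confidence interval lies inside it. This plan names none, and its Objective, the additional value of naprapathy, is a superiority question.

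At stake is what the trial may conclude from a non-significant result. Under the sentence as written, such a result would license the statement that naprapathy adds nothing on pain, motor function or EMG, even when the interval still contains the effect the investigators planned for. The printed β adds to the risk: a reader who takes β=.01 at face value would think that a real planned effect could be missed only 1% of the time, and would trust a declaration of no difference accordingly.

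**Working it through.** **Inputs.** From Sample Size: rates .75 and .55, α=.05, β=.01, 52 evaluable, 10% withdrawal, 58 per group. From Randomization: 1:1 allocation. Assumptions: a two-sided test of proportions as the main case, since neither sidedness nor a test for proportions is stated, and 52 read as per group. The text calls 52 a total, but only the per-group reading leads to the enrolled number: 52/0.9 = 57.8, rounded up to 58.

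**1. The plan's own figure.** The usual per-group formula is n = [1.96·√(2·p̄·q̄) + z(power)·√(p1·q1 + p2·q2)]² / (p1 − p2)², with p̄ = .65.

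- √(2·.65·.35) = .6745 and √(.1875 + .2475) = .6595.
- At 99% power (z = 2.326): (1.322 + 1.534)²/.04 = 204 per group.
- At 90% power: 118 per group. At 80%: 89 per group.

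The printed 52 is not reproduced. One-sided testing does not rescue it (175, 96 and 70 per group at the same three powers). The withdrawal step is reproduced.

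**2. Chance of P>.05 if 75% against 55% is true.** Power = Φ([.20·√n − 1.96·.6745]/.6595).

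- n = 52: (1.442 − 1.322)/.6595 = 0.182, power 57.2%, so P>.05 in 42.8%.
- n = 58: (1.523 − 1.322)/.6595 = 0.305, power 62.0%, so P>.05 in 38.0%.

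Other choices of test:

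| Test | P>.05 at 52 per group | P>.05 at 58 per group |
|---|---|---|
| Two-sided pooled z | 43% | 38% |
| Two-sided chi-square, exact enumeration | 41% | 38% |
| Two-sided Fisher | 50% | 45% |
| One-sided z | 31% | 27% |

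**3. What a non-significant result would still allow.** At the planned rates the 95% half-width for the difference is 1.96·√(.435/52) = .179, about 18 points (.170 at 58 per group). An observed difference of 10 points would then have an interval of roughly −8 to +28 points. It contains zero, so P>.05, and it also contains the planned 20 points. For a mean difference the half-width at 52 per group is about 1.98·√(2/52) = 0.39 SD.

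**4. The primary outcome.** The article gives no expected VAS difference and no SD, so step 2 cannot be repeated for it. Purely to show how far the answer depends on the missing input, power ≈ Φ(d·√(n/2) − 1.96) at 52 per group is 33% for a standardised difference d of 0.30, 53% for 0.40, 80% for 0.55 and 86% for 0.60. The chance of P>.05 therefore runs from 67% down to 14% over that assumed range.

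**The case against.** Several things can fairly be said on the other side.

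- *The low power is a separate fault.* It comes from a sample size that does not follow from its own inputs, and the misreading of P>.05 would be wrong at any power. This stands. The 38% to 43% illustrates the consequence and is not the ground of the point.
- *The figure does not belong to the primary outcome.* A reader might infer that the trial has about a 4 in 10 chance of missing its primary effect. The documents do not support that. The figure concerns the recovery rate used for sizing, the primary outcome is VAS change, and no VAS effect or SD is stated. Nor does the analysis section name a test for a recovery proportion.
- *Safety is not covered.* A reader might infer that the rule would also give false reassurance about adverse events. The safety paragraph plans only numbers of events and percentages of cases, with no between-group test, so the rule does not reach them.
- *Confidence intervals may be specified elsewhere.* This is a condensed article, and a fuller protocol or analysis plan may provide for them. Their absence here is not itself a fault, and Cohen *d* and the generalized linear model show that reporting is not confined to P values. But neither qualifies the sentence, which is stated wrongly rather than left out.
- *A misleading publication is not certain.* The authors may write up a non-significant result with more care than their plan requires. That is so; the point is only that the plan as written tells them otherwise.

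The Abstract's aim of giving reliable evidence for decisions contains no rule for reading P values and is not a second instance of the error.

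**Conclusion.** Wrong as written. Treating P>.05 as an indication of no difference is invalid in a superiority trial without an equivalence margin. The sentence applies to the primary VAS change and to the Brunnstrom and EMG outcomes. This conclusion rests on the wording alone and needs no assumption about power.

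The size can be illustrated for the sizing endpoint only. With a true 75% against 55% and a two-sided .05 test of proportions, the rule would label the planned effect absent in about 43% of trials at 52 per group and 38% at 58. Across one-sided and Fisher variants the range is 27% to 50%. All of these are far from the 1% that the printed β suggests. The corresponding risk for VAS is unknown.

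The sentence should be corrected. Doing so leaves the design and the primary test unchanged, but changes what may be concluded from a non-significant result.

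**What to change.** Replace the sentence on P values above .05 with:

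> If P≥.05, a difference has not been shown; the between-group difference and its 95% CI will be reported, and no claim of no difference or equivalence will be made.

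The plain between-group difference is enough, since the article defines no adjusted primary analysis. The wording also covers P exactly equal to .05, which the present text leaves out.

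The cost is one sentence, plus a report of the change to the ethics committee under the article's own rule on changes. No further participants, visits or measurements are needed. The Results section puts enrolment at 100 of 116 by January 2023, so the sample size was already largely fixed, whereas the rule for reading the result can still be changed at any time before the data are analysed.
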